### Interventions

All patients will undergo preoperative and postoperative investigations. Systemic examinations include routine blood tests, blood biochemistry, infection measurements (HIV, hepatitis B and C, and syphilis), chest computed tomography (CT), electrocardiography, and carotid Doppler ultrasound. Ophthalmic examinations include BCVA, slit-lamp, intraocular pressure, indirect ophthalmoscopy, FFA, and SD-OCT. The timeline of data collection is shown in Table 1.

**Table 1 Tab1:** Outcome measurements and data collection at each follow-up timepoint

Phase	Screen	Postoperative follow-up											
Follow-up	0	1	2	3	4	5	6	7	8	9	10	11	12
Time points	Before operation	1 month after operation	2 months after operation	3 months after operation	4 months after operation	5 months after operation	6 months after operation	7 months after operation	8 months after operation	9 months after operation	10 months after operation	11 months after operation	12 months after operation
Informed consent	●												
Inclusion and exclusion criteria	●												
Medical history collection	●												
Ophthalmic examinations													
BCVA	●	●	●	●	●	●	●	●	●	●	●	●	●
Slit lamp	●	●	●	●	●	●	●	●	●	●	●	●	●
Indirect ophthalmoscopy	●	●	●	●	●	●	●	●	●	●	●	●	●
IOP	●	●	●	●	●	●	●	●	●	●	●	●	●
SD-OCT	●	●	●	●	●	●	●	●	●	●	●	●	●
FFA	●						●						●
Laboratory examinations													
Routine blood test	●						●						●
Blood biochemistry	●			●			●			●			●
Infection measurements	●												●
Carotid doppler ultrasound	●			●			●			●			●
Electrocardiogram	●						●						●
Chest CT	●												●
Adverse events recorded	●	●	●	●	●	●	●	●	●	●	●	●	●

*BCVA* best corrected visual acuity, *IOP* intraocular pressure, *SD-OCT* spectral-domain optical coherence tomography, *FFA* fluorescence fundus angiography, *CT* computed tomography

### Outcome measurements

Monthly follow-ups will be performed after surgery in both groups. The necessary investigations will be conducted at each follow-up visit.

The outcome measurements include CSFT, BCVA, number of injections, and incidence of adverse events.

### Primary outcomes

The primary outcome is the average change in CSFT from baseline to 12 months.

### Secondary outcomes

Secondary outcomes are BCVA, average number of injections, and incidence of adverse events at each visit during the 12-month follow-up visit.

### Safety and combined operation-related adverse events

Possible operation-related complications include elevated intraocular pressure, endophthalmitis, traumatic cataract, vitreous hemorrhage, retinal hemorrhage, retinal detachment, and drug-related adverse events (e.g., liver function damage and gastrointestinal discomfort). In this trial, all the above adverse events and possible causes will be recorded and managed accordingly.

### Follow-up plan

Monthly follow-ups and necessary re-examinations after surgery will be conducted. BCVA, slit lamp, intraocular pressure, indirect ophthalmoscopy, and SD-OCT will be performed at each visit. Blood biochemistry and carotid Doppler ultrasonography will be performed every 3 months. Routine blood tests, FFA, and electrocardiograms will be performed every 6 months. Infection measurements (HIV, hepatitis B and C, and syphilis) and chest CT will be performed during the last visit. The number of injections and the incidence of complications will be recorded and evaluated at each follow-up.

### Re-injection criteria

If the BCVA drops by more than five Early Treatment Diabetic Retinopathy Study (ETDRS) letters (one line) or an increment in CSFT of 100 μm (or a 10% increment from the previous visit), intravitreal re-treatment will be performed.

### Sample size calculation

The sample size is estimated as follows: according to the results from our pre-experiment, the average CSFT in the control and experimental groups was 263.72 ± 30.63 μm and 241.17 ± 18.54 μm, respectively. The type I error rate (*β*) was set at 0.05, with 80% power at 5% significance and 1:1 randomization. *Zα* = 1.96, *Zβ* = 0.84, standard deviation (*σ*) in experimental group = 30.63, difference in means (*δ*) = 263.72 − 241.17 = 22.55.

Sample size $$n=\frac{2{\left({z}_a+{z}_{\beta}\right)}^{2\ast }{\sigma}^2}{\delta^2}=2\times {\left(1.96+0.84\right)}^2\times 30.{63}^2/22.{55}^2=29.$$

Thus, 29 patients will be required in each group. Considering a loss ratio of 10%, the total sample size will increase to 32 patients in each group.

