### Inclusion criteria

The inclusion criteria are as follows: (1) patients with a branch or central RVO, aged between 45 and 75 years old; (2) central sub-field thickness (CSFT) > 250 μm, best corrected visual acuity (BCVA) < 0.5; and (3) body mass index < 28 kg/m^2^, carotid stenosis without recanalization surgery.

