### Statistical analysis

Data from the patients’ clinical records will be processed using SPSS. For normally distributed data, continuous variables will be expressed as mean ± standard deviation, difference between groups will be evaluated by the Student’s *t*-test, and comparisons inter-group at each endpoint will be evaluated by repeated measures analysis of variance. The Bonferroni method will be used to adjust the overall significance level for multiplicity. For abnormally distributed data, continuous variables will be expressed as M (Q1, Q3), differences between groups will be evaluated using the Mann–Whitney *U* test, and comparisons between groups at each endpoint will be evaluated using a generalized linear mixed model. Categorical variables will be expressed as counts (%), and the chi-square test will be performed. The effect of missing data on the trial results will be assessed using sensitivity analyses of the augmented datasets. Dropouts will be included in the analysis by using modern imputation methods for missing data. The BCVA will be converted to the minimum resolution angle in logarithmic form before data analysis. The clinical data of the branch and central RVO will be sub-analyzed. Two-tailed tests of significance will be performed, and *P*-values < 0.05 will be considered statistically significant.

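### The 80% power is calculated for CSFT levels, but the declared primary outcome is change in CSFT from baseline, so the stated power does not describe the planned comparison

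*Protocol article*

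**What the plan says.** All places are in the protocol article.

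- **Primary outcomes:** "The primary outcome is the average change in CSFT from baseline to 12 months".
- **Sample size calculation:** "according to the results from our pre-experiment, the average CSFT in the control and experimental groups was 263.72 ± 30.63 μm", against 241.17 ± 18.54 μm in the experimental group. The effect is the difference of these two means, "263.72 − 241.17 = 22.55" μm. The SD entered is described as "in experimental group = 30.63", with z-values 1.96 and 0.84. The result is 29 per group, raised to 32 for 10% loss.
- **Statistical analysis:** for normally distributed data, groups are compared by Student's t-test, and "comparisons inter-group at each endpoint will be evaluated by repeated measures analysis of variance". For non-normal data, the Mann–Whitney test and a generalized linear mixed model are named. Tests are two-sided at 0.05.
- **Inclusion criteria:** "central sub-field thickness (CSFT) > 250 μm", with no upper limit.

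The sample size section gives no SD of change, no baseline SD, no correlation and no time point for the pre-experiment figures.

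**The concern.** The pre-experiment figures are levels, not changes. Read as reductions from baseline, they would give the control group the larger benefit. The experimental mean, "241.17 ± 18.54 μm, respectively", lies below the entry threshold of 250 μm, so it looks like a value after treatment.

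The outcome to be tested is a change. Its SD depends on the baseline SD and on the correlation between baseline and month 12, and neither enters the calculation. The 80% therefore belongs to a different quantity from the declared outcome. If baseline thickness varies more than treated thickness, an unadjusted comparison of change could have well under 80% power to detect the 22.55 μm difference that the trial is designed around. A null result would then be hard to interpret.

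**Working it through.** **Inputs from the protocol.** δ = 263.72 − 241.17 = 22.55 μm; SD 30.63 μm, which is the control group's SD of levels; two-sided alpha 0.05; 29 evaluable patients per arm.

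**Inputs not in the protocol (assumed, shown as a range).** Baseline SD s0 from 30.63 to 100 μm; correlation ρ between baseline and month 12 of 0.3, 0.5 and 0.7 for the change comparison. The month-12 SD is taken as 30.63 μm, the protocol's own figure. δ is kept at 22.55 μm, which carries over to change only if the pre-experiment groups were alike at baseline. The protocol does not say whether they were.

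**Step 1: reproduce the plan's figure.** n = 2 × (1.96 + 0.84)² × 30.63² / 22.55² = 28.93, so 29 per arm. Power at 29 per arm is 80.1% by the normal approximation and 78.7% by the noncentral t. The arithmetic is right for a comparison of levels.

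**Step 2: SD of the declared outcome.** SD of change = √(s0² + 30.63² − 2ρ × s0 × 30.63). This is no larger than 30.63 only if s0² ≤ 2ρ × s0 × 30.63, that is, ρ ≥ s0 / 61.26:

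- s0 = 30.63: ρ ≥ 0.50
- s0 = 45: ρ ≥ 0.73
- s0 = 60: ρ ≥ 0.98
- s0 above about 61: no correlation suffices

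**Step 3: power of an unadjusted t-test on change** (29 per arm, δ = 22.55, noncentral t; SD of change in brackets).

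| Baseline SD (μm) | ρ = 0.3 | ρ = 0.5 | ρ = 0.7 |
|---|---|---|---|
| 30.63 | 64% (36.2) | 79% (30.6) | 94% (23.7) |
| 45 | 45% (46.2) | 56% (39.8) | 75% (32.1) |
| 60 | 30% (58.6) | 37% (52.0) | 48% (44.3) |
| 100 | 14% (95.4) | 16% (88.7) | 18% (81.5) |

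Keeping all 32 per arm changes little: at s0 = 60 and ρ = 0.5, power is 40%.

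**Step 4: a smaller month-12 SD.** The pooled pre-experiment SD is √((30.63² + 18.54²)/2) = 25.32 μm. If baseline SD is also 25.32, the change SD stays within 30.63 once ρ is about 0.27 or more, so there is some slack. At s0 = 45 the slack is gone: power is 47% at ρ = 0.3 and 58% at ρ = 0.5.

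**Step 5: baseline-adjusted comparison.** With ANCOVA on baseline CSFT the residual SD is 30.63 × √(1 − ρ²), which does not involve s0: 30.63, 29.22 and 26.53 μm at ρ = 0, 0.3 and 0.5. Power with 29 per arm is about 79%, 82% and 89%.

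**The case against.** **The size is not in the document.** This stands. No baseline SD, correlation or SD of change is given, and the table includes cells where power is met or exceeded. A reader might infer that the trial is certainly badly underpowered, for example at 9% to 37%. Those figures need an assumed baseline SD of 60 to 150 μm with the correlation held at 0.5 or below. By the inequality in step 2, every scenario in that range must fail, so they cannot be presented as the expected power.

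**Open-ended entry does not prove a wide baseline.** This also stands. Untreated branch and central RVO above 250 μm with no ceiling makes a baseline SD above 30.63 μm plausible, but establishes no value. Nor does analysing change add the whole baseline variance as noise. The variance added is s0² − 2ρ × s0 × 30.63, which equals s0² only at ρ = 0.

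**The primary test is not pinned down.** The analysis section does not say in so many words that a t-test on change scores is the primary test. A t-test on month-12 levels would match the sample size calculation, but it is not the declared outcome. Repeated-measures ANOVA does not avoid the problem: with baseline as one of the time points, its group contrast for baseline to month 12 is the same comparison of change.

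**Covariates are commonly left to the analysis plan.** That is true, and the absence of a covariate is not itself the point. The point is that the stated outcome and the stated power inputs conflict, and an unseen plan cannot change what the published 80% was computed for.

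**Conclusion.** The inconsistency is established from the text: the calculation uses levels, the outcome is change, and the tests named do not bridge the two. The 80% does not describe the declared outcome.

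A loss of power is plausible but not proven. It depends on two quantities the protocol does not give. Power is kept if the baseline SD is about 30 μm and the correlation is 0.5 or more. It falls to between 30% and 48% at a baseline SD of 60 μm for correlations of 0.3 to 0.7. These figures assume a month-12 SD of 30.63 μm and a true difference of 22.55 μm. The adjusted-analysis figures rest on the same two assumptions, taken from a pre-experiment whose size and time point are not stated.

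Two labels in the sample size section are also wrong, without affecting n: 30.63 is attributed to the experimental group although it is the control SD, and the type I error is denoted β.

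**What to change.** 1. In the outcome and analysis sections, make the primary analysis an ANCOVA of month-12 CSFT with baseline CSFT as covariate, or the month-12 contrast of a mixed model with the same covariate. With baseline in the model, the adjusted group difference is identical whether the outcome is written as change or as level, so the declared outcome can stay.
2. In the sample size section, state that the 80% refers to this comparison and assumes a residual SD of at most 30.63 μm.
3. In the same edit, relabel 30.63 as the control-group SD and the type I error as alpha.

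The cost is wording in three sections. SD-OCT is already scheduled for every patient before treatment and at month 12, so no patients or procedures are added. The article reports 14 patients recruited at submission; the change should be documented as an amendment before any unmasked analysis.

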### Statistical analysis

Data from the patients’ clinical records will be processed using SPSS. For normally distributed data, continuous variables will be expressed as mean ± standard deviation, difference between groups will be evaluated by the Student’s *t*-test, and comparisons inter-group at each endpoint will be evaluated by repeated measures analysis of variance. The Bonferroni method will be used to adjust the overall significance level for multiplicity. For abnormally distributed data, continuous variables will be expressed as M (Q1, Q3), differences between groups will be evaluated using the Mann–Whitney *U* test, and comparisons between groups at each endpoint will be evaluated using a generalized linear mixed model. Categorical variables will be expressed as counts (%), and the chi-square test will be performed. The effect of missing data on the trial results will be assessed using sensitivity analyses of the augmented datasets. Dropouts will be included in the analysis by using modern imputation methods for missing data. The BCVA will be converted to the minimum resolution angle in logarithmic form before data analysis. The clinical data of the branch and central RVO will be sub-analyzed. Two-tailed tests of significance will be performed, and *P*-values < 0.05 will be considered statistically significant.

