**Methods and analysis:**

A prospective randomized controlled clinical trial will be conducted. Sixty-four patients diagnosed with branch or central RVO-ME and coexistent CP will be enrolled and randomly allocated in a 1:1 ratio to the control and experimental groups. The control group will be treated with intravitreal conbercept monthly for 3 months, followed by monthly evaluation and injection of pro re nata (PRN) for 12 months, while the experimental group will be treated with oral atorvastatin 20 mg daily combined with the control group treatment. If a drop of best-corrected visual acuity (BCVA) is more than five Early Treatment Diabetic Retinopathy Study (ETDRS) letters (one line) or an increment in central subfield thickness (CSFT) of 100 μm (or a 10% increment from the previous visit), intravitreal re-treatment will be performed. Outcome measurements include CSFT, BCVA, number of injections, and incidence of adverse events during the 12-month follow-up period. Differences between groups will be evaluated using Student’s *t*-test, and comparisons between groups will be evaluated using repeated-measures analysis of variance.

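### Repeated-measures ANOVA is assigned to the between-arm comparison at each endpoint, but its omnibus tests are not endpoint contrasts; a mixed model with a stated month-12 contrast would fit the aim better

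*Protocol article*

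**What the plan says.** All references are to the protocol article. Table 1 schedules BCVA and SD-OCT, which supplies CSFT, at baseline and at 12 monthly visits. Under Primary outcomes: "The primary outcome is the average change in CSFT from baseline to 12 months".

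For normal data, the Statistical analysis section names two methods. First, "difference between groups will be evaluated by the" Student's t-test. Second, "comparisons inter-group at each endpoint will be evaluated by repeated measures analysis of variance". The Abstract repeats the second: "comparisons between groups will be evaluated using repeated-measures analysis of variance". For non-normal data the second method changes: "comparisons between groups at each endpoint will be evaluated using a generalized linear mixed model".

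The same section adds "The Bonferroni method will be used to adjust the overall significance level for multiplicity", and on missing data "Dropouts will be included in the analysis by using modern imputation methods for missing data" and "The effect of missing data on the trial results will be assessed using sensitivity analyses of the augmented datasets". It does not say which term or contrast of the ANOVA gives the result at an endpoint.

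**The concern.** The stated aim is a comparison of the arms at each endpoint. With 12 or 13 visits, a classical repeated-measures ANOVA returns two tests that involve the arms:

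- **Group test.** It compares the arms on the mean over all visits. Those visits include the first three months, when both arms receive the same monthly injections, and baseline too if it is entered as a level.
- **Group-by-time test.** It asks whether the difference between arms varies over visits. Its nominal error rate needs sphericity, which monthly measurements rarely satisfy because neighbouring visits correlate more strongly than distant ones.

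Neither test says how far the arms differ at month 12. An analyst who reads the output as the answer at each endpoint may report a weak averaged result when the benefit is late, or an over-liberal interaction test when no correction is applied. The procedure also uses only patients with every visit. The data collected support a direct month-12 comparison, and the section already turns to a mixed model, but only when data are not normal.

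**Working it through.** **Inputs.** From Sample size calculation: difference 22.55 μm, SD 30.63, 29 per arm (32 with losses), two-sided 5%. From Table 1: 12 post-baseline visits, 13 with baseline. The article gives no correlation between visits, no course of the effect over time and no missed-visit rate; these are assumptions below.

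**1. The plan's own figure.** 2 × (1.96 + 0.84)² × 30.63² / 22.55² = 28.93, so 29 per arm, as stated. The trial is sized on a difference of two means. At one visit, 22.55 / (30.63 × √(2/29)) = 2.80 and Φ(2.80 − 1.96) = 0.80.

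**2. Error rates with no effect.** Simulation, 32 per arm, 12 visits, 4,000 runs, nominal 5%:

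| AR(1) | Group test | Group-by-time, uncorrected | Group-by-time, Greenhouse-Geisser | Month-12 contrast |
|---|---|---|---|---|
| 0.5 | 5.3% | 7.6% | 4.1% | 5.6% |
| 0.7 | 5.4% | 9.9% | 4.6% | 5.0% |
| 0.9 | 5.1% | 12.6% | 4.7% | 5.0% |

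Reruns with 6,000 replicates agree. Only the uncorrected group-by-time test is inflated.

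**3. Power of the group test.** The averaged difference is 22.55 times the mean of the effect profile. The SD of a patient's mean over T visits is 30.63 × √(sum of all correlations / T²). Power is Φ(difference / (SD × √(2/29)) − 1.96). Profiles, averaged over 13 visits including baseline:

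- linear from month 0: 22.55 × 6.5/13 = 11.28
- linear from month 3: 22.55 × 5/13 = 8.67
- full from month 4: 22.55 × 9/13 = 15.61
- full from month 1: 22.55 × 12/13 = 20.82

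The baseline-adjusted month-12 contrast uses SD 30.63 × √(1 − r²), where r is the correlation of baseline with month 12 (0.5, 0.8¹² = 0.069, 0.9¹² = 0.282).

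| Correlation | SD of mean | Linear from 0 | Linear from 3 | Full from 4 | Full from 1 | Month 12, adjusted |
|---|---|---|---|---|---|---|
| Compound symmetry 0.5 | 22.48 | 48% | 31% | 75% | 94% | 90% |
| AR(1) 0.8 | 20.97 | 53% | 35% | 81% | 97% | 80% |
| AR(1) 0.9 | 25.02 | 40% | 26% | 66% | 89% | 83% |

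Worked cell (AR(1) 0.9, linear from month 3): 8.67 / (25.02 × 0.2626) = 1.32; Φ(1.32 − 1.96) = 0.26. Simulations of these settings gave 26–53% for the group test under linear build-up and 76–89% for the adjusted month-12 contrast.

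The loss depends on the correlation. With linear build-up from month 0, the same formula gives 67% at AR(1) 0.7 and 87% at AR(1) 0.5. Leaving baseline out raises the averaged difference to 22.55 × 6.5/12 = 12.21, and power becomes 90%, 71% and 45% at AR(1) 0.5, 0.7 and 0.9.

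**4. Complete cases.** If visits are missed independently with probability p, 64 × (1 − p)¹² patients have all 12: 56.7 at 1%, 50.2 at 2% and 34.6 at 5%. This loss occurs only if single gaps are not imputed.

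**The case against.** The best defence is that the section can be read more kindly. It asks for comparisons at each endpoint and then names Bonferroni, which suggests adjusted by-visit contrasts within the repeated-measures model. It also names a t-test, and the sample size rests on one. Twelve Bonferroni-adjusted visit contrasts keep the familywise error at 2.3–4.3% in simulation. A sphericity correction is routine detail that an article may leave to the full protocol or analysis plan. This largely stands. What remains is that the named method does not itself supply the stated comparison, and the text does not tie Bonferroni to visit contrasts or say which method answers for month 12.

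A reader might infer more, in four ways that the article does not support:

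- **That the planned test is distorted.** Nowhere does the article say that an uncorrected group-by-time test will be used, and the other tests hold their level.
- **That patients with a missed visit will be dropped.** Imputation is planned for dropouts, and sensitivity analyses for missing data. Only single missed visits are left unnamed.
- **That averaging always costs power.** With a constant effect from month 1 it gains power in most settings. The month-12 figures in the last column also include the gain from baseline adjustment; unadjusted, month 12 has 80%. The primary outcome wording does not clearly exclude an average over time.
- **That the unequal pilot SDs (30.63 and 18.54) invalidate the ANOVA.** With 32 per arm and AR(1) 0.7–0.9, simulated error was 4.7–5.0% for the group test and 5.3–6.0% for the month-12 t-test. That is nearly harmless at 1:1 allocation, and a mixed model with one common covariance would not address it.

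**Conclusion.** The point holds as a poor match between method and aim, with a better method at hand. It is not a demonstration that the trial's conclusions would be wrong. The error inflation is confined to one test in one form. The power loss is large when the effect builds up late and visits are strongly correlated, smaller or absent otherwise, and reversed in most settings when the effect is constant from month 1. The loss of patients depends on the assumed missed-visit rate and on gaps staying unimputed. The sample size of 29, raised to 32 per arm, is not affected. The change is worth making before data are unmasked, because it fixes in advance which comparison carries the month-12 result.

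**What to change.** For CSFT and for BCVA, replace repeated-measures ANOVA with a linear mixed model for repeated measures of the post-baseline values. Include arm, visit, arm-by-visit, baseline value and baseline-by-visit, and use all observed visits. State the covariance structure and its fallback in advance: for example unstructured, then heterogeneous Toeplitz, then AR(1) with robust standard errors. Report the month-12 arm contrast with its confidence interval, and treat the other visits as descriptive. If the primary outcome is meant as an average over visits, say so; the same model gives that as a named contrast.

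The cost is a few lines of analysis text. The planned software fits linear mixed models, though the availability of robust standard errors in the chosen procedure should be confirmed. No extra patients, visits or unmasked data are needed, and 14 of 64 patients had been recruited at submission (Trial status). The downside is that an unstructured covariance over 12 visits has 12 × 13 / 2 = 78 parameters for 64 patients and may not converge. That is why the fallback must be stated, and a simpler structure can itself be misspecified.

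### No test is named as decisive for the primary CSFT outcome and Bonferroni has no stated family, so the 5% error and 80% power hold only on a reading the text does not give

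*Protocol article*

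**What the plan says.** Under Primary outcomes there is one variable and one horizon: "The primary outcome is the average change in CSFT from baseline to 12 months". The wording fits a mean change at month 12, but it could also be read as a change averaged over the visits.

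Under Statistical analysis, normally distributed continuous variables get Student's t-test for the group difference and repeated-measures ANOVA for inter-group comparisons at each endpoint. For data that are not normal, the Mann-Whitney U test replaces the t-test, and "comparisons between groups at each endpoint will be evaluated using a generalized linear mixed model". The abstract also lists the t-test for group differences and adds that "comparisons between groups will be evaluated using repeated-measures analysis of variance". Neither place says which result decides the primary outcome.

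On significance, the same section states: "The Bonferroni method will be used to adjust the overall significance level for multiplicity". It gives no family and no number of comparisons. It closes with "Two-tailed tests of significance will be performed" and the rule that P-"values < 0.05 will be considered statistically significant", without saying whether that P is adjusted.

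The Sample size calculation is "with 80% power at 5% significance and 1:1 randomization", with a Z of 1.96 and no allowance for multiplicity.

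**The concern.** Three statements have to fit together for the primary result to have one meaning: which test is used, at what level, and what the trial was sized for. The article fixes only the third.

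Read literally, adjusting the overall significance level includes the primary comparison, and the sample size made no provision for that. If Bonferroni is kept away from the primary comparison, two tests remain available for the same variable in the same data, and nothing says which one counts. A CSFT result could then be significant by one method or threshold and not by another, with the choice made after the data are seen. Which pair of tests applies also depends on how the data look.

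**Working it through.** **Inputs.** From the Sample size calculation: difference "263.72 − 241.17 = 22.55" μm, SD 30.63 μm, Z values 1.96 and 0.84, 29 per group, 32 after loss. From the follow-up schedule: 12 monthly visits with SD-OCT. Assumed, because the article does not give them: the number of Bonferroni comparisons k, and the correlation of CSFT between visits.

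**1. Reproduce the plan's figure.** n = 2(1.96 + 0.84)² × 30.63² / 22.55² = 15.68 × 938.20 / 508.50 = 28.93, so 29 per group. This matches the article, and confirms that the calculation covers one two-sided test at 0.05 with no adjustment.

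**2. Power at that size.** The noncentrality is 22.55 / (30.63 × √(2/29)) = 2.80. The normal approximation gives 80.1%. The exact noncentral-t value on 56 degrees of freedom is 78.7%.

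**3. If the primary comparison is in the Bonferroni family.** Replace 0.05 by 0.05/k and keep everything else.

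| k (assumed) | Level | Power, 29 per group, noncentral t | Power, 29 per group, normal approx. | Power, 32 per group, normal approx. | n per group for 80% |
|---|---|---|---|---|---|
| 1 | 0.05 | 78.7% | 80.1% | 83.8% | 29 |
| 2 | 0.025 | 69.1% | 71.3% | 75.9% | 36 |
| 4 | 0.0125 | 59.0% | 62.0% | 67.3% | 42 |
| 12 | 0.00417 | 43.5% | 47.5% | 53.2% | 51 |

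Here k = 2 is the smallest possible family, k = 4 is the number of listed outcomes, and k = 12 is the number of monthly visits. The last column is before any allowance for loss.

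The plan's SD is the larger of its two pilot SDs. With the pooled value, √((30.63² + 18.54²)/2) = 25.32, noncentral-t power at 29 per group is 91.5%, 85.9%, 78.8% and 65.6% for k = 1, 2, 4 and 12. The loss from adjustment remains, from a higher starting point.

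**4. If Bonferroni does not touch the primary comparison and either test may be claimed.** This was simulated under no treatment effect: 29 per group, 12 equally correlated normal visits, no missing data, 20,000 runs. Success is P < 0.05 on the month-12 t-test or on the ANOVA group effect (the comparison of patient means over the 12 visits).

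| Visit correlation (assumed) | Type I error, either test |
|---|---|
| 0.3 | 8.6% |
| 0.5 | 8.3% |
| 0.7 | 7.6% |
| 0.9 | 6.4% |

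Each test alone stays near 5%.

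**5. Freedom to choose between the t-test and Mann-Whitney.** Claiming on either at month 12 gives 5.6% to 6.1% in the same simulation, so this adds only about one point.

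**6. If one t-test at 0.05 is the primary test and Bonferroni applies only elsewhere.** Type I error is 5% and power is that of step 2. Nothing is misstated.

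**The case against.** The strongest reply is that step 6 is the natural reading. There is one primary outcome, the sample size is for one comparison of two means, the t-test is listed first, and the Bonferroni sentence directly follows the one on repeated-measures comparisons. P < 0.05 is also compatible with Bonferroni, as the overall level being protected or as the threshold for adjusted P-values. All of this stands. A reader might infer that either power or type I error must be wrong as stated, and the article does not support that.

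Three other strong readings also fail:

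- **Four tests compete for the same result.** They do not. The two pairs are alternatives, chosen by distribution.
- **Success could be claimed at any of the 12 visits.** Nothing in the article allows that rule, and the primary horizon is 12 months.
- **ANOVA would discard every patient who misses a visit.** The Statistical analysis section plans imputation for dropouts and sensitivity analyses for missing data, so a complete-case loss cannot be presumed.

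It can also be said that a condensed article may leave the Bonferroni family and the model to a fuller document. That would answer a bare omission. Here the article states a set of tests, an adjustment and a threshold, and leaves their bearing on the primary comparison open. The preference for a baseline-adjusted mixed model is a recommendation and does not correct a stated error.

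**Conclusion.** The point holds as an unresolved ambiguity about the primary analysis. It is not a demonstrated contradiction.

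Its size depends on how it is resolved. Including the primary comparison under Bonferroni would cut power at 29 per group from about 79% to between 69% and 43.5%, for an assumed k of 2 to 12. Leaving it out while accepting either of two tests would raise type I error to about 6% to 9%, for an assumed exchangeable visit correlation of 0.9 to 0.3. With one prespecified test at 0.05 the stated figures hold. The text should be changed so that this third case is what it says.

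**What to change.** Amend the Statistical analysis section, before anyone sees unmasked data, to say the following:

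- **Primary test.** The between-group contrast in CSFT at month 12, adjusted for baseline CSFT, from one linear mixed model over all visits. It is tested at two-sided 0.05 without Bonferroni, which matches the level in the sample size calculation.
- **No data-dependent switch.** This model is used whatever a normality test shows. A rank-based or log-scale analysis is added as a sensitivity analysis.
- **Bonferroni.** It applies to a stated family of secondary outcomes, with the number of comparisons given. P < 0.05 there refers to adjusted P-values.
- **Other visits.** Between-group comparisons of CSFT before month 12 are descriptive.

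If the sponsor does want the primary comparison inside the Bonferroni family, the sample size must be recomputed. On the plan's own inputs that means 36 to 51 evaluable patients per group for k from 2 to 12.

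The cost is a few sentences. No new data are needed, since CSFT is already measured at baseline and at every visit. The downside is fewer nominally significant claims.
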